## **1. INTRODUCTION**

### **1.1 Background and Rationale**

This study is part of a consortium-based clinical programme the aim of which is to develop and qualify novel safety markers of kidney, liver and vascular injury. The SAFE-T consortium is part of the Innovative Medicines Initiative and represents a collaboration between academic institutions, pharmaceutical companies and related small business enterprises, and the European Medicines Agency. The primary aim of this consortium is to develop novel safety markers that can be used both in drug development programmes to monitor organ safety as well as in hospital practice to identify patients at risk of organ injury or detect this injury at an earlier stage and therefore improve the prognosis by prompt intervention and treatment.

Blood urea nitrogen (BUN), serum creatinine and urinary protein (either by dipstick urinalysis or measuring urinary protein/ creatinine ratio) are currently used to monitor renal safety and to detect acute renal injury. Whilst these renal markers are highly specific, at least 50% of renal function may be lost before these markers are able to detect any injury. This can be seen in the case of live donors in renal transplantation where the donor's BUN and creatinine do not usually show any significant change from pre-operative levels. Furthermore, these markers do not usually change until 3 to 5 days after the injury. There is therefore a need for more sensitive markers to detect renal injury at a milder and earlier stage.

Cisplatin is a widely used and potent chemotherapy drug administered alone or in combination for the treatment of a number of cancers such as testicular, head and neck, ovarian, cervical and non-small cell lung carcinoma, amongst other [Pabla and Dong, 2008]. Its use is limited by adverse effects, notably nephrotoxicity. This occurs in about one-third of patient undergoing high dose cisplatin treatment. Clinically, nephrotoxicity is often seen within about 10 days of cisplatin administration and is manifested as lower glomerular filtration rate, higher serum creatinine, and reduced serum magnesium and potassium levels. It causes proximal and distal convoluted tubular damage by entering tubular cells and activating apoptotic pathways that result in cell death. It also induces the production of TNF, triggering a robust inflammatory response and further contributing to tubular cell injury and death. Cisplatin may also induce injury in the renal vasculature, leading to ischemic tubular cell death and decreased glomerular filtration rate (GFR). Together, these pathological events culminate in acute renal failure in a proportion of patients [Pabla and Dong, 2008].

### **1.2 Study Aim**

The primary focus of the study is to assess novel markers of renal safety. Stored samples from this study will also be available for future research in renal safety markers as well as those of other organ systems.

The study will enrol cancer patients who are scheduled to receive high dose cisplatin as monotherapy or as part of a combination chemotherapy regimen. The cisplatin treatment will be administered as part of the standard of care management of these patients' cancer; there will not be any change to patients' cancer treatment as a result of participating in this study. Control patients and healthy volunteers will be recruited for comparison purposes. Blood and urine samples will be collected at baseline and at various time-points after the first administration of cisplatin to assess the time-course

of any changes in the various novel renal injury biomarkers and compare these with BUN and serum creatinine changes.

## **2. STUDY OBJECTIVES AND ENDPOINTS**

### **2.1 Objectives**

- To collect blood and urine samples in cisplatin-treated patients and control subjects.
- To characterise the within- and between-subject baseline variability of novel biomarkers relative to BUN/ serum creatinine in these populations.
- To compare the patterns of novel biomarker changes relative to BUN/ serum creatinine following cisplatin treatment. These data will be used to:
  - select candidate biomarkers to progress to the confirmatory stage of biomarker qualification and establish cut-off values for these biomarkers.
  - determine the optimum method of expressing (corrected vs. uncorrected) each novel urinary marker relative to urinary creatinine for subsequent studies.
  - characterise the time course of biomarker changes to optimise the study design and sample collection time-points of confirmatory studies.

### **2.2 Endpoints**

- For each novel serum and urinary biomarker, as well as for BUN and serum creatinine, the following will be determined:
  - Maximum change from baseline.
  - Time to maximum change from baseline.
  - Once cut-off values are determined, time to abnormal change.
  - Time to return to baseline (or to return to normal range).
  - Mean change over period of observation (AUEC analysis)
- Novel urinary biomarkers will be assessed in the following ways in the various analyses of interest:
  - corrected for urinary creatinine concentration, and
  - uncorrected biomarker concentration.

## **3. STUDY DESIGN**

This is a prospective, non-randomised, longitudinal, case control study. Patients with cancer who are scheduled to receive high dose cisplatin as part of their standard of care treatment (e.g. non-small cell lung cancer, head & neck cancer) will be enrolled in this study. Control patients with similar cancers who have not had recent major surgery or treatment with nephrotoxic drugs will be enrolled as a control patient population. A cohort of healthy subjects will be enrolled as a separate healthy control population.

Subjects will have a screening assessment where their diagnosis and eligibility for enrolment is confirmed. The study will be explained to them and subjects willing to participate will be asked to give informed consent. Unless documented by clinical

chemistry laboratory results in the previous month, subjects will have a blood sample taken for BUN and serum creatinine to document baseline renal function and confirm they meet the criteria for the study. Eligible patients scheduled to receive cisplatin will have blood and urine samples taken pre-dose on the day of first cisplatin administration and at intervals over the next 3 weeks. Control subjects (cancer patients and healthy volunteers) will attend the clinic to give blood and urine samples at two visits that are 2 days (+/- 1 day) apart.

Enrolled subjects will have blood and urine samples collected for novel biomarkers at the following time-points:

Cisplatin-treated group:

- Pre-dose on day of 1st cycle cisplatin chemotherapy administration (baseline)
- Prior to leaving the clinic following cisplatin administration (or at approximately 8 - 12 hours post-dose for in-patients)
- 24 hours post-dose
- 2 days post-dose
- 4 days (+/- 1 day) post-dose
- 7 days (+/- 1 day) post-dose
- 14 days (+/- 3 days) post-dose
- 21 days (+/- 7 days) post-dose

Control groups (cancer patients and healthy volunteers):

- Visit 1 (within 3 weeks of Screening: this may be the Screening visit after subjects have given their informed consent. In this case, for those subjects who are subsequently found not to qualify for inclusion after lab results are available, stored samples will be discarded and not included in any analysis. Any subjects not included after Screening will not count towards the number of enrolled subjects for the relevant cohort even if samples are taken and later discarded.)
- Visit 2 (2 days [+/- 1 day] after Visit 1)

Note that apart from samples taken in the cisplatin-treated patients in the 12 hour period after cisplatin infusion, all blood and urine samples will be collected in the morning. All subjects will be asked to attend the clinic within a 2-hour window (chosen after consultation between the Investigator and the subject) at each visit as far as possible.

**Table 1: Schedule of Activities for cisplatin-treated group of patients**

| Cisplatin-treated patient group                   | Screening | Pre-dose | <12 hrs | 24 hrs | 2 days | 4 days | 7 days | 14 days | 21 days |
|---------------------------------------------------|-----------|----------|---------|--------|--------|--------|--------|---------|---------|
| Informed consent                                  | x         |          |         |        |        |        |        |         |         |
| Blood sample (5 mL) for clinical chemistry        | x         | x        | x       | x      | x      | x      | x      | x       | x       |
| Urine sample (10 mL) for urinalysis               | x         | x        | x       | x      | x      | x      | x      | x       | x       |
| Check subject eligibility                         | x         |          |         |        |        |        |        |         |         |
| Review adverse events and concomitant medications | x         | x        | x       | x      | x      | x      | x      | x       | x       |
| Enrol subject                                     |           | x        |         |        |        |        |        |         |         |
| Blood sample (10 mL) for serum        |           | x        | x       | x      | x      | x      | x      | x       | x       |
| Blood sample (10 mL) for plasma       |           | x        |         |        |        |        | x      |         |         |
| Urine sample (40 mL)                  |           | x        | x       | x      | x      | x      | x      | x       | x       |
| Ensure patient has oncology follow-up visit       |           |          |         |        |        |        |        |         | x       |

To analyse for DIKI biomarkers as listed in Table 3.

A plasma sample will be stored for future use for novel renal and other organ safety biomarkers.

**Table 2: Schedule of Activities for patient controls**

| Patient control group n=20                        | Screening  | Visit 1  | Visit 2
(2 days post V1) |
|---------------------------------------------------|------------------------|----------------------|-----------------------------|
| Informed consent                                  | x                      |                      |                             |
| Blood sample (5 mL) for clinical chemistry        | x                      | x                    | X                           |
| Urine sample (10 mL) for urinalysis               | x                      | x                    | X                           |
| Check subject eligibility                         | x                      |                      |                             |
| Review adverse events and concomitant medications | x                      | x                    | X                           |
| Enrol subject                                     |                        | x                    |                             |
| Blood sample (10 mL) for serum        |                        | x                    | X                           |
| Blood sample (10 mL EDTA) for plasma              |                        | x                    | X                           |
| Urine sample (40 mL)                  |                        | x                    | X                           |

To analyse for DIKI biomarkers as listed in Table 3.

These visits may be combined if subject gives informed consent

**Table 3: Schedule of Activities for healthy control group**

| Healthy control group n=20                        | Screening  | Visit 1  | Visit 2
(2 days post V1) | Visit 3
(14 to 28 d post V1) |
|---------------------------------------------------|------------------------|----------------------|-----------------------------|---------------------------------|
| Informed consent                                  | x                      |                      |                             |                                 |
| Blood sample (5 mL) for clinical chemistry        | x                      | x                    | X                           | x                               |
| Urine sample (10 mL) for urinalysis               | x                      | x                    | X                           | x                               |
| Check subject eligibility                         | x                      |                      |                             |                                 |
| Review adverse events and concomitant medications | x                      | x                    | X                           | x                               |
| Enrol subject                                     |                        | x                    |                             |                                 |
| Blood sample (10 mL) for serum        |                        | x                    | X                           | x                               |
| Blood sample (10 mL EDTA) for plasma              |                        | x                    | X                           | x                               |
| Urine sample (40 mL)                  |                        | x                    | X                           | x                               |

To analyse for DIKI biomarkers as listed in Table 3.

These visits may be combined if subject gives informed consent

This is an observational study. All patients in this study will receive treatment as per standard of care for their conditions. Patients in this study that develop BUN or serum creatinine changes following cisplatin treatment that qualify as acute kidney injury will be managed according to standard hospital treatment protocols.

## 4. SUBJECT SELECTION

### 4.1 Inclusion Criteria

#### *All subjects*

- Males and females  $\geq 18$  years of age.

#### *Cisplatin patients*

- Patients with documented cancer (e.g. head & neck or similar) who are scheduled to receive 1st cycle high dose cisplatin therapy ( $\geq 65$  mg/ m^2/ cycle).

#### *Control subjects*

- Patients with documented cancer (similar to patients due to be treated with cisplatin) who have received or are scheduled to receive non-nephrotoxic treatment modalities.
- A further group of healthy control subject will be enrolled for comparison.

### 4.2 Exclusion Criteria

#### *All subjects*

- Chronic kidney disease defined by microalbuminuria ( $>30$  mcg/ mg urinary creatinine) or eGFR  $<60$  mL/min/1.73m^2.
- Regular co-administration of any of the following within 7 days prior to screening until the last sample collection time-point.
  - creatine supplements
  - drugs known to alter tubular secretion of creatinine (e.g. trimethoprim, cimetidine).
  - Non-steroidal anti-inflammatory drugs (ibuprofen, diclofenac, naproxen; occasional use allowed).
- Major surgery from 1 month prior to screening until the last sample collection time-point.
- *NOTE:* patients needing to take diuretic, ACEi or ARB drugs may be enrolled and continue on these therapies but these patients will be analysed separately.
- Inability to comprehend, or unwillingness to follow, the study requirements including attendance at out-patient clinic visits and participation in laboratory testing as called for by the protocol.

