## 7. SAMPLE COLLECTION & HANDLING

10 mL blood (serum) and 40 mL urine samples will be collected at each visit for the following kidney biomarkers:

**Table 3:** Novel biomarkers to be measured in this study

| Type of biomarker                    | Biomarker name*                                      | Main significance                                                                                                                               |
|--------------------------------------|------------------------------------------------------|-------------------------------------------------------------------------------------------------------------------------------------------------|
| Functional biomarkers         | Microalbumin/Albumin                                 | Marker of impaired proximal tubular reabsorption                                                                                                |
|                                      | $\alpha$ -1 microglobulin                            | Marker of impaired proximal tubular reabsorption and indirectly of glomerular injury                                                            |
|                                      | Cystatin C                                           | Evaluation of glomerular filtration rate (serum)
Marker of impaired proximal tubular reabsorption and indirectly of glomerular injury(urine) |
|                                      | Urinary creatinine                                   | Marker of impaired proximal tubular reabsorption and indirectly of glomerular injury(urine)                                                     |
|                                      | Retinol Binding Protein-4 (RBP-4)                    | Marker of impaired proximal tubular reabsorption                                                                                                |
| Tissue injury leakage markers | N-acetyl- $\beta$ -D-glucosaminidase (NAG)           | Marker of proximal tubular injury                                                                                                               |
|                                      | Glutathione-S-transferase- $\alpha$ (GST- $\alpha$ ) | Marker of proximal tubular injury                                                                                                               |

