|                   | Clusterin                                         | Marker of tubular injury/regeneration (no apparent specific nephronal localization) |
|                   | Neutrophil gelatinase associated lipocalin (NGAL) | Marker of tubular (mainly proximal) injury                                          |
|                   | Trefoil Factor 3 (TFF3)                           | Marker of proximal tubular injury                                                   |
|                   | Osteopontin                                       | Marker of injury to distal regions of nephron                                       |
|                   | Tissue inhibitor of metalloproteinase-1 (TIMP-1)  | Marker of interstitial fibrosis and tubular injury                                  |
|                   | Connective Tissue Growth Factor (CTGF)            | Marker of interstitial fibrosis                                                     |
|                   | Interleukin-18 (IL-18)                            | Marker of inflammation                                                              |
|                   | Monocyte chemoattractant protein-1 (MCP-1)        | Marker of inflammation                                                              |

\* All biomarkers will be assessed in urine and Cystatin C and NGAL will additionally be assessed in plasma/serum.

A 10 mL EDTA blood sample will be taken at the baseline and Day 7 visits only. The plasma obtained from these samples will be stored for future use for novel renal and other organ safety biomarkers.

Additional the following parameters will be assessed in the 5 ml blood plus 10 ml urine for routine diagnostics.

|                 |                                                                                                        |
|-----------------|--------------------------------------------------------------------------------------------------------|
| Blood Chemistry | Total protein, Albumin, Creatinine, Urea
Sodium, Chloride, Calcium, Phosphate, Potassium, Magnesium |
| Urinalysis      | U-Kreat; U-Urea; Na, K, U-Protein, U-Albumin (Midstream)                                               |

**Table 4:** Type of Samples and Approximate Amount of Blood and Urine to be collected from Each Subject

| Test                      | Sample volume (mL) | Number of visits sampled |                | Total volume (mL) |                |

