## **9. DATA ANALYSIS/STATISTICAL METHODS**

### **9.1 Sample Size**

The maximum sample size for this multiple cohort observational study is 140 patient/subjects comprising;

- 100 patients in the cisplatin cohort to have a minimum of 20 subjects who show post-cisplatin BUN and serum creatinine changes that qualify as AKI.
- 20 patients in the patient control cohort.
- 20 subjects in the volunteer control cohort.

A sample size of 100 patients in the cisplatin cohort and 20 patients/subjects in each control cohort will enable a reliable assessment of the form of the statistical distribution for baseline values for each novel BM. In addition, a sample size of 20 cisplatin patients with AKI and 20 patients/subjects in each control cohort will enable an exploratory comparison between cohorts to detect patterns of difference in the BM profiles over time.

The sample size of the cisplatin-treated and the control cohorts may be adjusted during the course of the study based on interim analyses of novel biomarker patterns as well as the incidence of AKI as defined by BUN and serum creatinine changes in the cisplatin cohort.

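### Urinary albumin/creatinine is both an eligibility gate and a biomarker under study, so its baseline reference holds only for subjects who passed the screen and is biased low where control Screening and Visit 1 coincide

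*Protocol*

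**What the plan says.** The exclusion criteria for all subjects (Protocol 4.2) rule out "Chronic kidney disease defined by microalbuminuria", with a threshold of 30 expressed in "mcg/ mg urinary creatinine". An eGFR below 60 mL/min/1.73m² also excludes. The rule therefore acts on creatinine-corrected urinary albumin in all three cohorts.

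The biomarker table in Section 7 has "Microalbumin/Albumin" as its first entry, and its footnote says "All biomarkers will be assessed in urine". Section 2.2 has each urinary marker analysed both corrected and uncorrected for urinary creatinine. One of the two study forms of albumin is thus the same quantity as the eligibility variable.

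Section 9.1 says that 100 cisplatin patients and 20 subjects in each control cohort "will enable a reliable assessment of the form of the statistical distribution for baseline values for each novel BM". Neither 9.1 nor 9.2.1 treats albumin differently.

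For control Visit 1, Section 3 says "this may be the Screening visit after subjects have given their informed consent". The footnotes to both control schedules repeat this permission. Stored samples from subjects who then fail eligibility are discarded. Cisplatin patients are screened first and give a separate pre-dose baseline sample.

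**The concern.** A marker's reference distribution should come from measurements that did not decide who entered the study. For albumin this fails in two ways, which should be kept apart.

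First, every cohort is selected on screening albumin, so the baseline distribution describes subjects at or below 30 mcg/mg at screening. That is a defensible population, but Section 9.1 does not state the condition. A larger sample does not restore a tail that selection has removed.

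Second, where a control's Screening and Visit 1 are combined, the reported baseline comes from the visit that qualified the subject. An eligible subject whose value happened to be high that day is lost, while one whose value happened to be low stays. The reference is then too low even for the eligible population. The cisplatin baseline does not share this defect, so albumin is compared across cohorts selected in different ways.

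At stake are albumin's control reference, any cut-off built on it, and the stated between-subject variability.

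**Working it through.** The protocol gives no SD, correlation or share of screened subjects above 30 mcg/mg, so there is no figure of its own to reproduce. What follows is an illustration under stated assumptions.

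**Assumptions (not in the documents).** Log albumin/creatinine is normal, with between-subject SD 0.9 and within-subject SD s_w = 0.4 or 0.6. A share p of screened subjects exceeds 30: 5%, 10% or 20%.

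**Step 1, total SD and mean.** s_T = √(0.9² + s_w²), which is 0.985 for s_w = 0.4 and 1.082 for s_w = 0.6. The mean is μ = ln 30 − s_T·z(1−p). For p = 10% and s_w = 0.4: μ = 3.401 − 0.985 × 1.2816 = 2.139.

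**Step 2, 95th percentile at a combined Visit 1.** If the qualifying value is also the baseline value, the percentile is exp[μ + s_T·Φ⁻¹(0.95(1−p))]. For p = 10% and s_w = 0.4: Φ⁻¹(0.855) = 1.058, and exp(2.139 + 0.985 × 1.058) = 24.1 mcg/mg. For s_w = 0.6 it is 23.6.

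**Step 3, 95th percentile in a fresh sample from the same subjects.** This was simulated with 2 million subjects per setting, keeping those with a screening value of 30 or below and drawing a second value with the same subject effect.

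| Share above 30 | Combined Visit 1, 95th percentile | Fresh sample, same subjects | Fresh values above the combined-visit 95th percentile |
|---|---|---|---|
| 5% | about 21 | 23 to 25 | 6% to 7% |
| 10% | about 24 | 29 to 33 | 8% to 10% |
| 20% | about 26 | 35 to 44 | 11% to 14% |

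Ranges run from s_w = 0.4 to 0.6. The last column should be 5% for an unbiased reference. It shows the effect on a cut-off set at the control 95th percentile, a rule that the protocol does not state.

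**Step 4, cisplatin baseline.** A second simulation used log SD 1.0, 5% to 30% of screened subjects above 30, and a screening-to-baseline correlation of 0.6 to 0.8. A separate baseline sample keeps 0.82 to 0.97 of the unrestricted log SD, and 3% to 18% of enrolled baselines still exceed 30. The distribution is attenuated, not cut.

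**Step 5, corrected against uncorrected form.** In the same setting, with log SD 0.6 for urinary creatinine, one sample for screening and baseline, and 10% above 30, the log SD falls to 0.84 of its unrestricted value for the corrected form and 0.89 for the uncorrected form. The tilt is modest.

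**Step 6, drift from Visit 1 to Visit 2.** With a combined visit and no true change, the expected geometric mean ratio is exp[(1−ρ)·s_T·φ(z)/(1−p)], where ρ = 0.9²/s_T² and z = z(1−p). For p = 10% and s_w = 0.4: ρ = 0.835, and exp(0.165 × 0.985 × 0.1755/0.9) = 1.03. The rise is 3% to 7% at p = 10% and 6% to 12% at p = 20%. For 20 controls, the 95% confidence half-width of the log ratio is 2.093 × √2 × s_w/√20 = 0.26 to 0.40, a ratio of about 1.30 to 1.49. The drift is small beside that noise.

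**The case against.** The strongest reply is that excluding chronic kidney disease defines a sensible population for a study of acute injury, and that Section 2.1 asks for variability in the enrolled populations. A wider distribution in people with albuminuria is then irrelevant. This stands as far as eligibility goes. It does not answer the combined-visit problem, where the reference is biased for the eligible population itself.

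A reader might infer that the rule also truncates albumin's cut-off, its ROC estimates and the corrected-versus-uncorrected choice. The documents do not support this. Section 2.1 lists the aims to set cut-offs and to "determine the optimum method of expressing (corrected vs. uncorrected) each novel urinary marker relative to urinary creatinine for subsequent studies" as uses of the changes after cisplatin. The sensitivity, specificity and 80% ranking in 9.2.1 concern prediction of DIKI. The exclusion rule does not limit post-dose values, so these analyses are affected only modestly, through baseline.

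Three further replies have weight:

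- Eligibility would presumably be judged from the routine urinalysis ("U-Kreat; U-Urea; Na, K, U-Protein, U-Albumin (Midstream"), while the biomarker is assayed from the separate 40 mL sample. The two results from one visit need not be identical, so the cut falls near 30 rather than exactly at it, and the Step 2 figures are the limiting case.
- Albumin is not unique. The eGFR criterion also selects on renal function, which bears on serum creatinine, the comparator.
- The choice of reference visit could be left to a statistical analysis plan, and the analyses are exploratory. However, the unqualified claim in 9.1 and the permission to combine visits are both fixed in the protocol.

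**Conclusion.** The point holds in a limited form and at low severity. The Section 9.1 statement on baseline distributions is too broad for urinary albumin, because Section 4.2 selects on that quantity. For controls whose Screening and Visit 1 coincide, the albumin reference is also biased low within the eligible population: about 24 against 29 to 33 mcg/mg at the 95th percentile if 10% of screened subjects exceed 30, but only about 21 against 23 to 25 if 5% do.

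These sizes rest on assumed SDs, on the assumed share above 30, and on the qualifying and baseline values being the same measurement. The effect also depends on how many controls combine the visits, which the documents leave open. With 20 subjects per control cohort an upper percentile is imprecise in any case, but unlike that imprecision the bias would not shrink with more controls. Baseline in the 100 cisplatin patients is attenuated rather than cut.

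**What to change.** In Sections 9.1 and 9.2.1, state that albumin's baseline distribution, and any cut-off derived from a reference distribution, are conditional on a screening albumin/creatinine of 30 mcg/mg or below. For controls with combined Screening and Visit 1, take the albumin reference distribution from Visit 2, which did not decide eligibility.

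Visit 2 urine is already scheduled for both control cohorts, so no extra sample, visit or patient is needed. The eligibility criteria, the 80%/80% ranking and the corrected-versus-uncorrected comparison can stay as they are. The cost is a less favourable, conditional statement for one marker and a different reference visit for some controls.
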